## Discussion

Real-world studies with PR programmes in low-resource settings have evaluated the evolution of functional capacity and QoL of home-based programmes without support equipment [19, 57]. Such studies concluded that a home-based PR programme, using minimal resources and little direct supervision, delivers improvements in functional exercise capacity and HRQoL that are at least equivalent to conventional centre-based PR in people with COPD [19, 57]. Not providing equipment to participants is a methodological option since the objective of this study is to evaluate effectiveness, which differs from efficacy. We want to evaluate an intervention in the real-world context, where people do not all have access to the necessary equipment and still have to continue living with their disease, developing their own strategies with the nurse’s guidance. It is essential to set realistic goals so that COPD patients start slowly and gradually increase the duration and intensity of their workouts over time. Self-monitoring is vital so that patients can identify the symptoms related to the risk of complications [4, 43].

According to the study design, we expect to observe that the home-based PR programme brings clinically relevant benefits to the participants at the end of the first eight weeks and that, at 12 months, after the maintenance phase of the programme, the benefits obtained after the eight weeks fade away slower than individuals who do not have the programme maintenance phase.

It is also expected that patients experience fewer COPD exacerbations.

### Main potential biases

The intervention is unlikely to be blinded, which can be considered biased.

Another aspect that could bias our study is the Hawthorne effect throughout the study (i.e. behaviour change in participants due to their involvement in the study). However, establishing a cohort time of one year will not sustain this effect. On the other hand, the control group (“usual care”) will maintain their usual care with their assistant doctors, who are entirely free from any influence of the study design. With this approach, the Hawthorne effect will not contaminate the control group and represent usual real-life care.

Moreover, we also expect some attrition bias, considering the length of the follow-up and the need for complete adherence to the study protocol, mainly the intervention. Nevertheless, by increasing the sample size to a potential loss to follow-up up to 20%, we expect to overcome it.

Another potential bias is related to our inclusion/exclusion criteria. Since we excluded patients with complex and critical comorbidities, we cannot extend our conclusions to the general COPD population. However, this ensures a proper and exact evaluation of the intervention’s potential benefit. That might, to some extent, apply to those patients as well.

We expect that this work will contribute towards the preservation of the benefits obtained after a classic PR programme (8-weeks), through implementation of a maintenance component. At the same time we expect to increase the availability of this essential treatment to COPD patients and to identify the characteristics of the patients who benefit the most from home-based programmes.

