### Sample size and statistical methods

The minimum sample size required was calculated considering the final comparison between the two groups regarding the primary outcome and the inclusion of five covariates to adjust for potential comparison biases between the groups.

We will perform an intention-to-treat analysis. Therefore, stipulating ANCOVA as the statistical procedure to be used, a significance level of 5%, a test power (1-β) of 80%, an average effect magnitude (f = 0.25, corresponding to $$\eta$$^2^= 0.06, 6% of the variability of the dependent measure under evaluation to be explained by the group) and five covariates in the model, the sample size to be collected will be 128 participants, which corresponds to 69 participants for each group.

Considering that we may have 20% follow-up losses, the sample size to be collected will be 160 participants (80 per group).

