### Data analysis

The sample size covers the sample dimension necessary for applying a mixed ANCOVA. The group will be considered an inter-subject factor, the time/intervention (four moments) as the intra-subject factor, and the five covariates. This analysis will test the main and interaction effects between these two factors.

We also aim to carry out the described procedure using only the three moments T1, T2, and T3 and consider T0 an additional covariate. We will proceed with their decomposition if significant time or interaction effects exist.

Finally, a latent growth model will be tested to assess the trajectory (linear and quadratic) of the study participants concerning outcomes and how this trajectory is conditioned by the factors that originate the groups.

Statistical analysis will be performed using IBM SPSS Statistics V28 and IBM SPSS Amos V28, and p values < 0.05 will be considered significant.

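### Enlarging the sample for 20% loss protects power only; it cannot overcome the attrition bias the protocol expects, and the mixed ANCOVA as named does not make up for that

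*Protocol article*

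**What the plan says.** Three sections of the protocol article bear on this.

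- **Sample size and statistical methods.** The principle is stated as "We will perform an intention-to-treat analysis". The trial is sized for an ANCOVA with "a significance level of 5%, a test power (1-β) of 80"%, f = 0.25 and "five covariates in the model, the sample size to be collected will be 128 participants". The allowance for dropout follows: "Considering that we may have 20% follow-up losses, the sample size to be collected will be 160 participants (80 per group"), up from the 128 above.
- **Data analysis.** This section names the method and ties it to that calculation: "The sample size covers the sample dimension necessary for applying a mixed ANCOVA". Group is the between-patient factor and time, with four moments, the within-patient factor. A second run uses T1, T2 and T3 with T0 as a covariate. A latent growth model comes last. The section does not say how a patient with a missing visit enters the mixed ANCOVA.
- **Main potential biases.** Some attrition bias is expected. The reasons given are the length of follow-up and the adherence required, chiefly to the intervention. The remedy offered is that "by increasing the sample size to a potential loss to follow-up up to 20%, we expect to overcome it".

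**The concern.** The last statement treats a problem of bias as a problem of numbers. Recruiting more patients replaces the information lost with dropouts. It does not change which kinds of patient are lost, so a larger sample with the same selective loss has the same bias and a narrower confidence interval around it.

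The protocol gives its own reason to expect loss to differ by arm. Only the intervention arm has the maintenance schedule of visits and calls (8 + 16 + 20 = 44 weeks, section Intervention), while controls return to usual medical follow-up.

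The named method adds to the difficulty. A classical repeated-measures ANCOVA needs a complete set of outcomes for each patient. Someone who misses only the seven-month visit (T2) is dropped even if the 12-month walk distance (T3) was measured. Without imputation, the analysed set is then smaller than the randomised set that the intention-to-treat statement implies. At stake is the between-arm comparison of 6-minute walk distance, the primary outcome.

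**Working it through.** **1. Reproduce the plan's figures.** Inputs from the sample size section: alpha 0.05, f = 0.25 (d = 0.5 for two equal groups), two groups, five covariates. Power is taken from the noncentral F distribution with df = (1, N − 7) and noncentrality N × f².

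| N | Power |
|---|---|
| 127 | 79.8% |
| 128 | 80.1% |

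The smallest adequate N is 128, as printed. For dropout, 128 / 0.80 = 160, also as printed. The enlargement is 160 / 128 − 1 = 25%; the 20% is the assumed loss. As a power allowance this is correct. (Separate slip: 128 is 64 per group, not the printed 69, which would make 138.)

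**2. Does bias depend on N?** Suppose patients lost from an arm are on average s SD worse than those who stay. The completers' mean then exceeds the mean of the whole arm by loss × s. For the unadjusted difference between arms:

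bias = loss(I) × s(I) − loss(C) × s(C)

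N does not appear. Assumed values, averaging 20% loss, with the same s in both arms:

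| Loss, intervention v control | s = 0.25 | s = 0.5 | s = 1.0 |
|---|---|---|---|
| 20% v 20% | 0 | 0 | 0 |
| 25% v 15% | 0.025 SD | 0.05 SD | 0.10 SD |
| 30% v 10% | 0.05 SD | 0.10 SD | 0.20 SD |

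For example, 0.30 × 0.5 − 0.10 × 0.5 = 0.10 SD, which is 20% of the planned 0.5. In this pattern the bias favours the intervention.

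**3. Check by simulation.** Assumptions: four visits, correlation 0.7, no true effect, about 21% lost overall (31% intervention, 12% control), low performers leaving the intervention arm, complete cases analysed with adjustment for T0.

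| N randomised | Spurious effect (SD) | False-positive rate |
|---|---|---|
| 128 | 0.070 | 8.1% |
| 160 | 0.069 | 8.7% |
| 320 | 0.071 | 12.0% |
| 1,600 | 0.073 | 43.1% |

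The spurious effect does not shrink as N grows, and the false-positive rate rises. With the same dropout mechanism in both arms the estimate was about 0.00 SD, with 5.1% rejections at N = 160.

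**4. A pattern that runs the other way.** Assumptions: true T3 difference 0.50 SD, 20% lost after T2 in each arm, at random in the intervention arm and driven by T1-T2 decline in controls, correlation 0.5-0.8. The complete-case T3 difference adjusted for T1 is about 0.40-0.45 SD, depending on how strictly decline determines loss. The bias is 0.05-0.10 SD, or 10-20% of the true effect, towards the null. An analysis that also uses the observed T2 values, under missing at random, returns about 0.50. If both arms share the decline-driven mechanism, the complete-case result is also about 0.50.

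**5. Missed T2 visits.** The 20% allowance covers loss to follow-up. If a further 5% miss T2 (assumed), 160 × 0.80 × 0.95 = 121.6, so about 121 complete cases remain. Power at 121 is 77.8%, against 80.1% at 128.

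**The case against.** Four points can be made for the plan.

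- **Complete-case deletion is not stated.** A reader might infer that the protocol commits to analysing only patients with every visit, so that intention to treat has already been abandoned. The text does not say this. Deletion follows from how the classical method works when nothing is imputed, and imputation rules may stand in an analysis plan that is not shown. This objection stands, so the conflict with intention to treat is conditional, and silence on missing data is not the finding. It does not rescue the statement that a larger sample overcomes the bias, which is wrong whatever that plan contains.
- **The latent growth model could use incomplete records.** It can be fitted by likelihood to patients with missing visits. But it is listed last, and the protocol does not offer it as the answer to attrition.
- **The bias may be nil.** This is true when loss and its relation to outcome are the same in both arms. A reader might take the figures above as a forecast. They are not: the documents give no dropout pattern by arm, and decline in controls as a cause of loss is an assumption made here.
- **The loss of power is small.** A reader might also count missing T1 values and arrive at fewer complete cases. The section Assignment of interventions places the T1 assessment at randomisation (though it also ties allocation to consent), and the arms diverge only after the shared eight weeks. Missing T1 among randomised patients is therefore not a fair assumption. With T2 alone at risk, the shortfall is about two percentage points.

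**Conclusion.** The claim in Main potential biases is wrong as written. The step from 128 to 160 is a correct allowance for power and has no effect on attrition bias. The mixed ANCOVA, run in its classical form without imputation, would not supply the missing protection and would undercut the intention-to-treat promise by dropping patients whose T3 was measured.

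The size and direction of any bias are unknown. Under assumed patterns it ranges from zero, through 0.05-0.10 SD towards the null (selective loss in controls only), to as much as 0.20 SD in favour of the intervention (30% v 10% loss, dropouts 1.0 SD worse). The effect on power is minor: about 78% instead of 80% if 5% of those otherwise followed miss T2. The error in the claim rests on no assumption; the sizes rest entirely on the assumptions listed.

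**What to change.** 1. In Main potential biases, say that the enlargement for 20% loss protects power only, and delete the claim that it overcomes attrition bias.
2. Base the primary intention-to-treat estimate on a likelihood-based mixed model (MIXED in the SPSS package already named): T2 and T3 as outcomes, group-by-visit, T0 and T1 as covariates, including every randomised patient with any post-T1 value. Multiple imputation before the mixed ANCOVA would also serve.
3. Seek the T3 assessment from patients who stop the programme. This has to be arranged while follow-up is running, because it cannot be recovered afterwards.
4. Add one sensitivity analysis for data missing not at random, since both options in step 2 assume missing at random.

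The cost is a few sentences of protocol text, some effort to bring back patients who have left the programme, and a little more analysis work. Neither the sample size nor the software changes.

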## Data Availability

No datasets were generated or analysed during the current study.

## Abbreviations

PR: Pulmonary rehabilitation
COPD: Chronic obstructive pulmonary disease
HRQoL: Health-related quality of life
MUST: Malnutrition Universal Screening Tool
SARC-F: Strength, Assistance in walking, Rise from a chair, Climbing stairs, and Falls score
mMRC: modified Medical Research Council
CCQ: Clinical COPD Questionnaire
CAT: COPD Assessment Test
HADS: Hospital Anxiety and Depression Scale
FRR: Functional respiratory re-education
PLB: Pursed-lips breathing
HR: Heart rate
HRR: Heart rate reserve
